## Abstract

**Background:**

Total knee arthroplasty (TKA) is a surgical procedure primarily used to treat patients with end-stage knee osteoarthritis (KOA). Postoperative physical exercise is a critical part of the overall treatment of KOA and can bring significant benefits to the patients' recovery. Wearable devices can monitor patients' exercise data and upload it to the physician's workstation. This allows the rehabilitation physician to make timely adjustments based on the patients' movement feedback, and the surgeon can be informed of the patients' functional status. Overall, this study aims to evaluate the effectiveness of using wearable monitoring devices for rehabilitation exercise after TKA, with a focus on cost, time savings, and patient outcomes.

**Method/design:**

This is a single-center, single-blinded, parallel randomized controlled trial conducted at Xi'an Honghui Hospital, a regional orthopedic medical center. Eligible patients will be recruited to participate in the study, and baseline data collection and clinical assessments will be conducted at the time of admission. Using the principle of random allocation, recruited patients will be divided into either the experimental or control group. Both groups will undergo a standard, widely promoted rehabilitation program. The patients in the experimental group will wear equipment to detect and track mobility in the lower limbs. All patients will return to the outpatient clinic for follow-up assessments at 2 weeks, 12 weeks, and 24 weeks after discharge, where outcome indicators will be measured. The primary outcome will be the cost and time after discharge, while secondary outcomes will include the 6-min walk test (6MWT), range of motion (ROM), visual analog scale (VAS), American Knee Society Score (KSS), the Western Ontario and McMaster Universities Osteoarthritis Index (WOMAC).

**Discussion:**

We should encourage the adoption of novel, easy-to-use, supervised devices if they prove to be beneficial for patients in terms of cost, time, and effectiveness after TKA. This type of device is particularly important for people in remote rural areas, those with limited financial resources, and those who are reluctant to return to hospitals for follow-up care.

*Trial registration* Chinese Clinical Trial Registry ChiCTR2300068418. Registered on 17 February 2023.

**Supplementary Information:**

The online version contains supplementary material available at 10.1186/s13018-023-03898-z.

## Background

Osteoarthritis (OA) is a gradually advancing musculoskeletal disease that frequently affects the knee joint [1]. It is a debilitating condition and the primary indication for TKA [2]. TKA is a reliable surgical intervention for end-stage KOA [3, 4] and is recognized as a cost-effective treatment option [5]. The prevalence of TKA surgery has been increasing worldwide over the last 2 decades [6]. The rise in surgical procedures has imposed a substantial burden on healthcare budgets. Moreover, these surgeries are often accompanied by an extended rehabilitation period, significantly augmenting the costs of care [7].

Rehabilitation exercise after TKA is a critical component of a comprehensive KOA treatment plan and it can enhance patients' function, prognosis, and quality of life [8]. The rehabilitation program includes joint mobility exercises, such as range of motion, as well as exercises aimed at improving walking ability (posture, gait, and stability) and peripheral muscle strength [9]. The success of TKA relies on the effectiveness of postoperative rehabilitation and subsequent functional recovery [10]. Nowadays, home-based rehabilitation exercise, whether supervised or unsupervised, is considered a preferable choice for patients post-discharge due to its convenience [11–13]. Recent studies have revealed comparable outcomes between supervised physical exercise conducted at outpatient facilities and unsupervised exercise performed at home following TKA [14–18]. Systematic reviews and meta-analyses have further confirmed that supervised rehabilitation exercise does not provide any additional benefits [19, 20]. Hence, reducing costs and improving care efficiency are important objectives in rehabilitation programs [21]. Home-based rehabilitation offers a lower cost of care, aligning with this objective [22].

Wearable micro-sensing devices have become commonplace in the sports industry for real-time performance analysis of athletes [23, 24]. For instance, in the case of total hip arthroplasty and cardiovascular risk factors, accelerometry can be employed to monitor physical activity levels and estimate calories and energy expenditure by tracking movement patterns, including steps taken and distance traveled [25–27]. However, their potential use in healthcare has yet to be fully realized [28]. The number of studies on wearable motion sensors has grown in recent years, with many focused on knee replacements, providing additional information to clinical metrics [29]. This study aims to evaluate the cost, time savings and effectiveness of an innovative treatment approach using a new, simple monitoring device in conjunction with a mobile phone app to guide patient rehabilitation exercise. We hypothesize that patients in the experimental group would exhibit improved short-term functional outcomes and experience cost and time savings compared to patients in the control group.

## Methods/design

### Study design

This is a randomized controlled trial conducted at Xi'an Honghui Hospital. Patients are randomly assigned to one of two groups. The experimental group wears rehabilitation data acquisition devices and follows the APP guidance for exercise, while the control group follows the standard rehabilitation program. Both groups receive the same treatment regimen, rehabilitation exercise, and nursing services during hospitalization. Outcome assessments are conducted at 2w, 12w, and 24w after discharge, and the study flowchart is presented in Fig. 1. The study adheres to the Standard Protocol Items: Recommendations for Interventional Trials (SPIRIT) checklist, as provided in Additional file 1.

**Fig. 1 Fig1:**
[figure not shown]
Proposed CONSORT diagram

### Recruitment

Xi'an Honghui Hospital is a leading orthopedic center in China. The research team will provide patients with detailed information on the purpose, content, possible risks, and benefits of the trial, in adherence with the principle of informed and voluntary consent. The study will involve patients with end-stage KOA. Following completion of pre-operative preparations, TKA will be performed. The baseline registration and clinical evaluation conducted upon admission. During hospitalization, all patients receive the same treatment regimen and are discharged within 2–4 days after surgery.

### Inclusion criteria

The inclusion criteria for this study are as follows: (1) patients between 50 and 80 years old, (2) patients with end-stage knee osteoarthritis (KOA) who have been admitted to the hospital for TKA surgery, and (3) obtaining informed consent.

### Exclusion criteria

On the other hand, the exclusion criteria are: (1) patients who underwent surgical treatment of the lower limb within 6 months before or 3 months after this surgery, (2) patients with serious medical conditions that could affect exercise or outcome assessment, such as cerebral infarction, heart failure, or blood diseases, (3) patients with psychological disorders or neurological problems, (4) patients with cognitive deficits or language problems that would hinder their understanding of the study protocol, and (5) patients who refuse to participate.

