### Interventions

During their hospitalization, both the experimental and control groups receive the same treatment regimen, rehabilitation exercise, and nursing services. After undergoing TKA, patients in the experimental group are given wearable devices and are guided to perform rehabilitation training using an APP, while patients in the control group follow a handbook for their exercise program. The rehabilitation programs for both groups are consistent and were developed in accordance with the American Academy of Orthopaedic Surgeons (AAOS) Clinical Practice Guidelines (CGPs), the American Association of Hip and Knee Surgeons (AAHKS) guidelines, and other published literature [9, 32–34]. The rehabilitation exercise program can be found in Additional file 2. Following their discharge, both groups perform the home-based exercise program for 12 weeks. The patients in the experimental group will be required to return the devices to the research team at the 12th week. Following that, both groups of patients will no longer be required to adhere to the rehabilitation program's exercise regimen.

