### Primary outcome

The primary outcome measures of this study are the cost and time spent on medical care within 12 weeks after discharge. This includes costs for transportation, consultations, mobility aids, imaging examinations, and medications, as well as the time spent during the medical visit. All costs and time are recorded in a diary. Each entry in the diary must include the date, expenses, and time spent, along with the reasons. The diary is provided to the patients in both groups by the physiotherapists before discharge for free. The unit of cost is RMB, and the unit of time is hours.

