### Data analysis

The study schedule is depicted in Table 1. Data of all patients are recorded in Excel format and imported into SPSS (version 26.0; Armonk, New York, USA) for statistical analysis. To minimize bias due to missing data, intention-to-treat analyses and multiple imputation methods are employed. Descriptive statistics of measurement data are presented as mean ± standard deviation, while counting data are expressed as rate and composition ratio. Continuous variables are subjected to Student's *T* test if they meet the normal distribution, and Wilcoxon rank sum test is used otherwise. Categorical variables are tested using the chi-square test or Fisher's exact test. Secondary analyses are adjusted for baseline characteristics using analysis of covariance (ANCOVA). This study involves conducting multiple hypothesis tests, which undoubtedly increases the probability of Type I errors significantly. To control for family-wise error, Bonferroni corrections are adopted, resulting in a lowered adjusted *p* value of 0.002.

**Table 1 Tab1:** The patients’ schedule of trial enrollment, interventions, and assessment

Time point	Study period					
	Inpatient			Outpatient		
	Enrollment	Allocation	Pre-operation	2w	12w	24w
Enrollment						
Eligibility screen	×					
Informed consent	×					
Allocation		×				
Rehabilitation education			×			
Interventions						
Experimental group			×			
Control group			×			
Assessments						
Basal demographics and clinical data			×			
Cost					×	
Time					×	
6MWT						
ROM						
VAS						
KSS						
WOMAC						

“×” indicates the execution of the project according to the schedule

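### Exclusion criterion (1) reaches 3 months past the index operation, so eligibility depends on a post-randomisation event and conflicts with the stated intention-to-treat analysis

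*Protocol article*

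**What the plan says.** Exclusion criterion (1) in the protocol article covers "patients who underwent surgical treatment of the lower limb within 6 months before or 3 months after this surgery". The verb is in the past tense, and nothing limits the later window to operations already scheduled at enrolment.

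Table 1 in the Data analysis section marks the eligibility screen under Enrollment, gives Allocation the next column, and puts Pre-operation after that. The Interventions section says "After undergoing TKA, patients in the experimental group are given wearable devices", and that after discharge "both groups perform the home-based exercise program for 12 weeks".

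The primary outcome is "cost and time spent on medical care within 12 weeks after discharge", recorded by patients in a diary. Its content is described as follows: "This includes costs for transportation, consultations, mobility aids, imaging examinations, and medications, as well as the time spent during the medical visit".

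For the analysis, the plan states that "intention-to-treat analyses and multiple imputation methods are employed". The Randomization and blinding section says that patients and physicians know the allocation and only the data analysts are blinded. The Exit criteria section lists certain adverse events, infection and fracture among them, as reasons for leaving the study. It does not name further surgery.

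**The concern.** An eligibility rule should use only what is known before allocation. The post-operative part of this one cannot be assessed at screening. It therefore either has no effect, or it is applied later, to patients who are already randomised and on treatment.

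If it is applied later, three things are at stake:

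- **Comparability of the arms.** Randomisation balances the patients allocated, not the subset who later avoid surgery. The experimental arm sends exercise data to the physicians' workstation and can upload pictures of swelling and wounds, while the control arm works from a handbook. Detection of problems, and so the rate of further surgery, could plausibly differ between the arms.
- **The primary outcome.** A further operation brings consultations, imaging, medication, transport and visit time, which are the items the cost and time outcome counts. Excluding on that event removes part of what the trial sets out to measure.
- **Who decides.** The exclusion would be made by staff who know the allocation. Blinding the analysts does not protect against it.

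**Working it through.** The plan gives no figure for this point. The main check compares time windows; two illustrations follow.

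**1. Order of events.** From Table 1: eligibility screen, then allocation, then the pre-operative stage. The operation comes next, and the devices are handed out after it. The whole 3 months after surgery therefore follows allocation. Table 1 may be imperfectly reproduced in the text, but the conclusion does not hang on its exact columns: if allocation came after the operation and before discharge, nearly all of the window would still follow it.

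**2. Overlap with the primary outcome.** Discharge is 2 to 4 days after surgery (Recruitment section). Treatment and the primary outcome run for 12 weeks from discharge.

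- End of the primary window: 12 × 7 = 84 days, plus 2 to 4 days = day 86 to 88 after surgery.
- End of the exclusion window: 3 months, about 91 days after surgery.

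The exclusion window contains the entire treatment and primary outcome period.

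**3. Compatibility with the analysis.** Intention-to-treat keeps every randomised patient in the arm allocated; a patient reclassified as ineligible after a later operation leaves that set. Multiple imputation does not settle the conflict. It addresses missing values, whereas a patient with later surgery who keeps the diary has observed cost and time.

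**4. What would drive a bias (illustration on assumed inputs).** Let *p_E* and *p_C* be the proportions with further surgery in the experimental and control arms, and *C* the mean excess in recorded cost of such patients over the others, taken as equal in both arms. Keeping them, each arm mean is *m + pC*; excluding them, it is *m*. Exclusion therefore takes *C*(*p_C* − *p_E*) out of the control-minus-experimental difference. The documents give none of these inputs. Assuming *C* between 5,000 and 20,000 RMB and a 3-point difference in rates:

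- 5,000 × 0.03 = 150 RMB, and 150/2000 = 7.5% of the planned difference
- 20,000 × 0.03 = 600 RMB, and 600/2000 = 30%

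The sign reverses if the experimental arm has more surgery, and the shift is zero if the rates are equal. This shows how the bias arises; it is not an estimate.

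**5. Power (secondary).** The inputs are SD 3987, difference 2000 and two-sided 0.05 (Sample size section), with power = Φ(2000 / (3987 × √(2/n)) − 1.96). The section's own formula gives n = 83.5, so 84 per group against the stated 80. That is a separate, minor point and no evidence for this one. At n = 80 the power is 88.7%. If an assumed 2%, 5% or 10% of 100 per arm were excluded before dropout:

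| Excluded | 20% dropout | 25% dropout |
|---|---|---|
| 0% | 88.7% | 86.7% |
| 2% | 88.1% | 86.0% |
| 5% | 87.1% | 84.9% |
| 10% | 85.3% | 83.0% |

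The loss is modest. Bias is the concern.

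**The case against.** The best defence is that the criterion is only loosely worded. Table 1 shows a single eligibility screen, at enrolment, with no later re-screen. Departures after entry have their own section, and further surgery is not listed there. A rule applied only at enrolment can act only on surgery already expected, such as a staged operation on the other knee, and the plan does commit to intention-to-treat.

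That reading is plausible, and part of it stands: a reader might infer that patients will in fact be deleted from the analysis, and the documents do not establish that. What they establish is a rule which, as written, permits it. The text refers to surgery undergone, not surgery planned, so even on the milder reading the sentence needs changing.

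Three stronger readings also fail:

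- **That further surgery is itself a trial outcome.** It is in neither the primary nor the secondary list. It feeds the cost and time outcome through the care it generates, and whether operation charges count is not stated.
- **That the rule would remove the costliest patients and inflate the saving by a known amount.** The documents give no rate, cost or direction.
- **That the sample size has no room for such losses.** The Sample size section allows for 20–25% dropout and loss. The margin is tight (80/0.80 = 100 per arm at 20%), but it exists.

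A further objection is also sound: changing this criterion alone does not keep every such patient in follow-up, because infection and fracture remain exit criteria.

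**Conclusion.** The point holds as a wrongly fixed rule, not as a missing detail. Criterion (1) makes eligibility depend on an event after randomisation, its window spans the whole treatment and primary outcome period, and applying it would contradict the plan's own intention-to-treat statement. This rests on the wording of the criterion and on allocation preceding discharge; it needs no assumed figures.

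The size and direction of any bias cannot be derived from the documents. The 150 to 600 RMB illustration rests wholly on assumed costs and an assumed 3-point difference in rates, and it could run either way. The rule should be corrected before the first patient is randomised. The Trial status section says the trial had not begun at protocol version V1.1, so at that version nothing stands in the way.

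**What to change.** 1. In criterion (1), delete the part that extends to 3 months after the operation. If staged surgery was the reason for it, restrict that part to lower-limb surgery already planned before randomisation.
2. In the Data analysis section, state that every randomised patient with later lower-limb surgery stays in the intention-to-treat analysis in the allocated arm, with diary-recorded cost and time counted as the Primary outcome section defines them. This adds no new cost component.
3. Reconcile this with the Exit criteria section, so that leaving the exercise programme after an adverse event does not mean removal from the analysis, and diary data are still sought where the patient agrees.
4. Optionally, add a sensitivity analysis without patients who had later surgery, labelled as conditioning on a post-randomisation event.

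The cost is one line in the eligibility criteria and a sentence each in two other sections. No new instrument is needed, only continued diary collection to week 12 from patients who might otherwise have been dropped. The downside is slightly more variable cost data.

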### Exit criteria

The exit criteria for this study are as follows: (1) patients may withdraw from the study at any time without providing a reason, (2) patients experiencing adverse events such as wound dehiscence, infection, fracture, or pulmonary embolism, and (3) patients lost to follow-up. Any reasons for exit are recorded and reported to the ethics committee.

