### Experimental group and equipment components

The patients will require assistance from the doctors to download the APP and connect the devices. The devices consist of two small monitors, which are placed about 5 cm above and below the knee joint when exercising the knee joint, and about 5 cm below the knee and the dorsum of the foot when exercising the ankle joint (refer to Fig. 2). These devices can monitor the magnitude and completion of exercises and then upload the data to the physicians' workstation. Patients can watch instructional videos on the APP to learn how to wear and exercise with the devices and then start exercising actively. The APP provides prompts for exercise frequency and whether the exercise target is reached by voice. Patients can view their exercise progress on the APP, such as the completion rate and compliance rate. Additionally, they can upload their own functional and symptomatic information to the APP, such as lower limb swelling, ecchymosis, and wound healing, in the form of videos or pictures.

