### Ethics and dissemination

The study will adhere to the principles of the Declaration of Helsinki and Good Clinical Practice. The study protocol has been approved by the Ethics Committee of Xi'an Honghui Hospital (No.202301012) and registered in the Chinese Clinical Trial Registry (Registration Number: ChiCTR2300068418). The committee, which is independent of the research team, will oversee the trial's conduct. The research team will explain the study's purpose and methods in detail to potential participants or their authorized agents and obtain written informed consent from them. The team will also strictly safeguard the patients' data. Patients participating in the study have the right to discontinue their involvement at any time and without providing any reason, or the study may be discontinued if a clinician deems the patients unfit to continue due to other complications. Any adverse events will be reported to the ethics committee, and medical advice and assistance will be provided to the subjects. The trial data will be available to the subjects, and the results will be published in a journal.

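### The exit rule for adverse events ends study participation without keeping the cost and time diary going, so the primary outcome is lost when an event is likely to raise it

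*Protocol article*

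**What the plan says.** All references are to the protocol article.

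- **Exit criteria.** The list concerns leaving the study and begins "The exit criteria for this study are as follows: (1) patients may withdraw from the study at any time without providing a reason". The second item is "patients experiencing adverse events such as wound dehiscence, infection, fracture, or pulmonary embolism"; the third is loss to follow-up. Reasons for exit are recorded and reported to the ethics committee. Data collection after exit is not mentioned.
- **Primary outcome.** "The primary outcome measures of this study are the cost and time spent on medical care within 12 weeks after discharge". The content is given as "This includes costs for transportation, consultations, mobility aids, imaging examinations, and medications, as well as the time spent during the medical visit", and the source is the patient: "All costs and time are recorded in a diary".
- **Data analysis.** "To minimize bias due to missing data, intention-to-treat analyses and multiple imputation methods are employed".
- **Ethics and dissemination.** A further route out: "the study may be discontinued if a clinician deems the patients unfit to continue due to other complications".
- **Exclusion criteria.** The first item also covers lower-limb surgery in the 3 months following the index operation, which cannot be known at enrolment.
- **Experimental group and equipment components.** Patients in this arm can send information on their condition to the APP, "such as lower limb swelling, ecchymosis, and wound healing, in the form of videos or pictures".

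**The concern.** The adverse-event item stands between voluntary withdrawal and loss to follow-up, two ways in which observation normally ends, and it is worded as exit from the study rather than from the exercise programme. Read as written, measurement stops because of an event that is itself likely to cause the care being measured. The protocol, not the patient, then creates the missing data, and the reason for missingness is tied to the unseen value.

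Both primary outcomes are affected, as are the functional assessments at 2, 12 and 24 weeks that fall after exit. Exit may also differ between arms. Only the experimental arm sends in wound images and symptom reports, so complications could be found or averted at a different rate there. If monitoring saves money partly by avoiding complications, or adds cost through them, that part of the effect is what the rule leaves unmeasured.

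**Working it through.** **1. Is there a figure in the plan to reproduce?** None for this point: the article gives no adverse-event rate and no cost per event. The related figures are in the Sample size section: SD 3987, difference 2000 RMB, two-sided alpha 0.05, power 0.9, 80 per group, 200 in total. The stated formula gives

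n = 2 × (1.960 + 1.282)² × 3987² / 2000² = 83.5, so 84 per group.

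The plan's 80 is not reproduced. At 80 per group the power is 88.7% by the normal approximation. That gap is a separate matter; 84 serves below only as the baseline for step 5.

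**2. The sections side by side.** Intention-to-treat for a 12-week total needs the 12-week total from every randomised patient. The exit rule ends participation at the event, and no section continues the diary or visits. Diary entries made before exit would exist; the remainder of the 12 weeks would not.

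**3. What multiple imputation can do.** Under missing-at-random, the missing part is predicted from patients who are alike on observed data. If every patient with a listed event exits, nobody with an event has observed post-event cost. Event status in the model then has no data from which to estimate its effect, and the imputed values resemble those of event-free patients.

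**4. Size of the loss.** Let pC and pE be the event rates in control and experimental, and XC and XE the excess cost per event that goes unrecorded. All are assumptions.

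- Mean cost understated by pC × XC in control and pE × XE in experimental.
- Part of the control-minus-experimental difference that is lost: pC × XC − pE × XE. With a common excess X this is (pC − pE) × X.

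| pC | pE | X (RMB) | Lost from difference (RMB) | Share of 2000 |
|---|---|---|---|---|
| 6% | 3% | 10,000 | 0.03 × 10,000 = 300 | 15% |
| 5% | 3% | 5,000 | 0.02 × 5,000 = 100 | 5% |
| 5% | 3% | 20,000 | 0.02 × 20,000 = 400 | 20% |
| 3% | 5% | 10,000 | −0.02 × 10,000 = −200 | −10% |
| 5% | 5% | 10,000 | 0 | 0% |

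A positive value means the saving is understated, a negative one that it is overstated. In the last row the difference is unbiased, but each arm's mean is too low by 0.05 × 10,000 = 500 RMB.

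**5. Effect on spread.** If a fraction p has an added cost X, independent of the rest, the events contribute an SD of X × √(p(1 − p)). Taking 3987 as the SD without events:

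- p = 5%, X = 10,000: event SD 2,179; total √(3987² + 2179²) = 4,544; the formula gives 109 per group, and 80 per group has 79.5% power.
- p = 5%, X = 20,000: event SD 4,359; total 5,907; the formula gives 184 per group, and 80 per group has 57.2% power.

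In the second case the event part alone exceeds the planning SD. Either so large an excess is unrealistic for the listed cost items, or the planning SD comes from data without such patients. The article does not allow a choice between these.

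**The case against.** The strongest reply is that the article is silent on data handling after exit and condenses a fuller protocol. It does not say that exited patients are dropped from the analysis set, and the imputation model would belong to an analysis plan that is not shown. This stands in part: the loss of post-event data follows from the rule as worded and is not an explicit statement. But the rule itself is in the text, and no analysis plan can recover data that the protocol has stopped collecting.

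Several stronger readings are tempting and are not supported:

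- *That no intention-to-treat estimate can be obtained.* Exited patients can remain in the analysis set with imputed values. The difficulty is that the missing-at-random assumption becomes doubtful.
- *That the between-arm difference is biased in any case.* With equal rates and equal excess costs it is not.
- *That a device which causes or prevents complications would look neutral on cost.* Only the event-driven part is lost, and because exit reasons are recorded, exits can be counted by arm and bounds set.
- *That the removed patients are the most expensive.* This is a reasonable inference from the cost items, but the article does not say so, and readmission and reoperation are not named among those items.
- *That exit will differ by arm because of the image uploads.* This is possible but not shown. Fracture or embolism may be evident in either arm, and both arms attend the same scheduled visits.

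**Conclusion.** The concern holds as a conflict between a stated exit rule, the definition of the primary outcome and the intention-to-treat aim. The rule as written creates informative missing data on cost and time. If no patient with an event is followed, each arm's mean cost and spread are understated, and the difference is biased to the extent that event rates or event costs differ between arms, in either direction.

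The size is unknown. The 300 RMB (15% of target) example rests on an assumed 3-point difference in rates and an assumed 10,000 RMB excess, with all of that excess unrecorded; partial diaries would reduce it. The conflict does not depend on these figures. It should be settled before recruitment, which the Trial status section says has not begun, because the data cannot be rebuilt afterwards.

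**What to change.** 1. In Exit criteria, state that an adverse event does not end data collection. The diary continues to 12 weeks and the 2-, 12- and 24-week assessments continue. Event-related cost and time are counted in the arm as randomised. Only withdrawal of consent for data collection, or actual loss to follow-up, ends it.
2. Reconcile this with the exclusion for lower-limb surgery after the index operation and with the discontinuation text under Ethics and dissemination, so that neither removes randomised patients from follow-up or analysis.
3. Use multiple imputation only for data that are truly missing, with event status in the model. Once some patients with events are followed, that term can be estimated.
4. Leave decisions about the exercise programme to the clinical sections; this change concerns data collection only.

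**Cost.** An amendment to the wording; the diary and visits already exist. The real price is precision. Retained high-cost patients raise the SD of cost, possibly well above 3987, so the stated power may be lower. The sample size should be rechecked against an SD that includes patients with events; the 109 and 184 per group above show the sensitivity and are not estimates.
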